### **Intervention:**

The HIV CTR control condition includes case manager services to provide referrals to drug treatment, educational employment, and social services. Typically these services at the community correctional program sites are provided in 4 or fewer contacts. After an initial intake and case management referrals couples who are assigned to the HIV CTR control condition at randomization will receive a handbook of services designed for drug-involved male offenders to ensure that they have received basic service information. In addition, all couples assigned to HIV will receive Respect Brief HIV/STI pre-test or post-test counseling and referrals at their baseline visit. Providing evidence-based HIV/STI testing, counseling and referrals to all control participants at baseline will not only improve scientific rigor of the study but also ensure that the HIV CTR control condition meets ethical standards as a comparison group. At all assessments, data will be collected on number and type of visits and any other service or information received from participants and court records to monitor intensity and implementation of common elements of HIV CTR.

The PACT condition is delivered in community correctional program sites. Male offender participants who are assigned to PACT will also continue to receive regular services. The intervention is conducted by trained study staff. PACT addresses both drug and sexual risks with the following core components: (1) couple-based HIV Counseling Testing and Referral (CTR), (2) disclosure of drug and sexual risks; (3) couple communication, negotiation, and problem-

solving skills to reduce drug and sexual risks; (4) technical condom use skills; (5) strategies for reducing unsafe injections; (6) biomedical HIV prevention strategies (HIV treatment as prevention, PEP, PrEP; (7) linkage to HIV, STI and substance use treatment; (8) reproductive health issues (9) risks and experiences of sexual coercion, (10) risks for opioid overdose; (11) informal social support; and (12) couple goal setting to reduce long-term HIV risks.

PACT is designed to be educational, engaging, and tailored to the realities of drug-involved couples in CCP settings, through role play scenarios that highlight skills needed to face common challenges (e.g., coping with mandates and stigma). Sessions last one hour and will be conducted twice a week with the same case manager. For each session, couples will use a resource manual to help them identify and prioritize their HIV/STI, drug abuse and other service needs and to link them to appropriate services using a web-based program with an action plan for service engagement for each session.

### **Recruitment, Screening and Eligibility:**

Trained RAs will approach male clients at CCP sites after they are sentenced and give them flyers about the study. If a man is receptive, the RA will describe the study and answer any questions. If the man indicates that he is interested in the study, the RA will obtain consent to be screened, conduct a screening interview to determine eligibility and willingness to participate. The screening interview will contain eligibility related items, socio-demographics, and other items that will camouflage the eligibility criteria. Once the potential participant's eligibility has been established, he will be asked to invite his main female sexual partner to participate. If a potential participant and his partner inform the RA that they agree to participate, both are consented and screened. If the couple meets eligibility criteria, the RA will schedule the couple for a baseline assessment. We will provide monetary compensation to participants for completing the screening and all assessments

Eligibility Inclusion Criteria: Couples are eligible to participate if: (i1) both partners were aged 18 or older; (i2) both partners identified each other as their primary sexual partner of the opposite sex; (i3) the relationship had lasted at least 3 months; (i4) at least one partner reported having had condomless vaginal and/or anal intercourse with the other in the past 90 days; (i5) at least one partner reported exposure to an outside HIV risk in the past year (i.e., engaged in unprotected sex with another partner, shared syringes, tested positive for an HIV/STI) or at least one partner suspected that their partner had sex with another partner, injected drugs, was HIV positive or had tested positive for an STI ; (i6) the couple planned to stay together for at least another year; (i7) the male partner reported either (a) use of illicit drugs or binge drinking (i.e. drinking 5 or more alcoholic beverages) in the past 90 days or (b) attended substance abuse treatment in the past 90 days; and (i8) the male partner was mandated to community supervision, alternative to incarceration or probation verified by court records.

Eligibility Exclusion Criteria: Couples are excluded if: (e1) either partner shows evidence of significant psychiatric, physical or neurological impairment that would limit effective participation as confirmed during informed consent; (e2) either partner reported an order of protection within the past year or identified any safety concerns about participating in sessions with their partner; or; (e3) either partner did not have sufficient fluency in English.

Rationale for Eligibility Criteria: This study includes HIV positive, HIV negative, and HIV serodiscordant couples as this intervention has been designed for and tested with mixed status couples with a focus on dyadic strategies to keep HIV negative partners from seroconverting and to promote HIV treatment and ARV medication adherence among HIV positive partners. The study is limited to heterosexual relationships because our couple-based research with men who have sex with men indicate that gender roles and risk environments are likely to substantially differ.

### **Overview of subject participation:**

In the initial contact, a research assistant (RA) will administer consent and screen potential participants and their partners to determine their potential eligibility. Those couples deemed eligible are scheduled for the baseline visit, within 30 days of the initial screening. At the baseline visit, after the couple's eligibility is reconfirmed and the RAs administer the informed consent. Participants are then escorted to a private room and given instructions on the Audio Computer Assisted Self-Interview (ACASI) by the RA. After the baseline ACASI interview is completed, the RA conducts individual pre-test counseling for HIV and STIs and post-test counseling for HIV to each participant. Specimens are then collected, stored and shipped. The Clinical Research Coordinator will notify each participant privately of his or her STI test results within 7-10 days of the baseline visit, provide post-test counseling, and refer to STI treatment (if applicable). Within 1-10 days of their baseline visit, couples will be randomized to PACT or the HIV CTR control and the first PACT session will occur. Couples assigned to the HIV CTR control will receive a service handbook and service referrals. Intervention sessions 2-4 for PACT are implemented twice weekly at the CCP sites. The 3-month follow up will take place within 80-110 days of the last intervention session, which could range from 10-14 days post randomization for PACT condition. For the HIV CTR control condition, this date will be set at 12 days post randomization (mid midpoint of this range). The 6-month assessment will occur within 180 to 210 days of the last session. The 12-month assessment will take place within 360-390 days of the last session. At each follow up assessment, participants complete the ACASI interview. At the 6 and 12-month assessments biospecimens will be collected to test for STIs. At the 12-month follow-up, HIV negative participants will be retested for HIV.

### **Retention:**

We employ several steps to ensure retention from first point of screening to final 12-month follow-up that we have used successfully in previous research with drug-involved offenders under community supervision, including (1) providing compensation for assessments and reimbursing participants for transportation at each intervention session; (2) collecting detailed locator information, contacting participants before each session, and maintaining biweekly contact with participants during the follow-up period; (3) tracking participants who are incarcerated or in drug-treatment..

### **Assessment:**

Primary outcomes include indicators of sexual and drug risk based on self-reported behaviors and objective biological assay for STIs. We utilize a modified RBA to capture different types of sexual behaviors with study partners as well as with all other partners in the past 90 days. Secondary outcomes of drug use, access to drug treatment and other services, and recidivism will

be based on self-report and public court records. Intervention mediator and moderator measurements are based on self-report, organizational level data collected from CCP management staff, frontline providers and/or administrators. GIS community level data will be collected using zip code or census tract data from publically available databases. Service mapping of all drug treatment, social services and HIV prevention, testing and treatment services in NYC will be regularly updated in GIS data set. These instruments have been used in the baseline ACASI interview will take 75 minutes on average for participants to complete and the follow up assessments will take 40 minutes.

#### Assay for HIV, chlamydia, trichomonas and gonorrhea

For biological assays for HIV, we collect an oral specimen using OraQuick ADVANCE Rapid HIV. For chlamydia, trichomonas and gonorrhea, women self-collect a vaginal swab specimen and men provide a urine specimen. Specimens are assayed and tested for Chlamydia trachomatis and Neisseria gonorrhoeae using the Becton Dickinson Probe ET Amplified DNA Assay (Becton, Dickinson and Co, Sparks, Maryland) and for Trichomonas vaginalis using a real-time polymerase chain reaction assay.

Costs are estimated based on material purchase/consumption and time recorded regularly as part of project records. Additional data necessary for cost calculations, such as salary and capital costs (e.g., rent), will be obtained during administrative review, performed annually to account for inflation, from figures available and obtained by the Center for Court Innovation and the NYC Dept. of Probation.

#### **Data Analyses:**

The analytic approach is built upon the investigative team's prior HIV prevention randomized clinical trials. An intention-to-treat approach will be used. To enhance the rigor of an intention-to-treat analytic approach, we will employ multiple imputation to handle missing data, attrition analyses to investigate non-ignorable nonresponse, and sensitivity analyses to ascertain robustness of findings against violation of model assumptions (e.g., distribution requirements, heteroscedasticity, independence). Multiple imputation will be implemented using the imputation by chained equations algorithm (ice) in the statistical software Stata. This procedure allows specifying linear regression to impute continuous variables, logistic regression to impute dichotomous variables, multinomial logistic regression to impute categorical variables, and negative binomial regression to impute count data. Specifications of the imputation model will be based on the information that is observed or measured for a participant at prior assessments to predict values for variables that are missing, including covariates from the baseline assessment and behavioral outcome variables at the baseline and each follow-up assessment. The analysis plan is also informed by earlier RCTs of couple-based interventions. Generalized Linear Mixed Models (GLMM) will be used to account for the non-independence in measures arising from: (1) "autocorrelation" due to repeated measures with the same person; and (2) "intraclass correlation [ICC]" arising from partners who are reporting on conjoint behaviors. These models build upon  $g(E[(Y_{ij} | \mathbf{x}_{ij})]) = \mathbf{x}'_{ij} \boldsymbol{\beta}$  where  $Y_{ij}$  is the outcome variable of interest for the  $i$ th participant at the  $j$ th timepoint. The multilevel nature of the data are accounted for by modeling each predictor variable's coefficient in the vector  $\boldsymbol{\beta}$  as dependent on couple membership:  $\beta_i = \mathbf{w}_g \boldsymbol{\gamma}$  where the  $i$ th participant is part of the  $g$ th couple which determines the couple characteristics (i.e., elements of the vector  $\mathbf{w}$ ) used to estimate model fit parameters in vector  $\boldsymbol{\gamma}$ . The components of  $\boldsymbol{\beta}$  will be

treatment assignment, baseline attributes for the outcome variable, and those variables selected during preliminary analyses as noted earlier. The  $g(a)$  function represents a link function that can properly model the outcome variable as a function of measurement unit or distribution. Hypothesis testing follows the form “Assignment to PACT will be associated with significantly lower/higher on outcome variable Y at the 12-month follow-up compared to assignment to HIV CTR” where ‘lower’ or ‘higher’ is chosen in the direction of reduced risk. Outcome-specific modeling information for hypothesis testing is presented in Table 1.

| Table 1: Data Analytic Approach for Hypotheses Testing                                                                                                                                                                       |                                                        |                                                                   |                                                                                                      |
|------------------------------------------------------------------------------------------------------------------------------------------------------------------------------------------------------------------------------|--------------------------------------------------------|-------------------------------------------------------------------|------------------------------------------------------------------------------------------------------|
|                                                                                                                                                                                                                              | Y                                                      | Candidate* link function
g(a)                                  | Covariates used to
estimate $\beta$ & $\gamma$                                                    |
| H 1                                                                                                                                                                                                               | • Incidence of Chlamydia,
trichomonas and gonorrhea | • Logistic:
$\log(a/(1 - a))$
• Poisson: $\log(a)$          | • Baseline
attributes for
sociodemographics

• Attribute(s) of Y
measured at baseline |
| H 2                                                                                                                                                                                                               | • # of acts of unprotected
intercourse              | • Poisson: $\log(a)$
• Negative Binomial:
$\log(a/(k + a))$ |                                                                                                      |
| H 3                                                                                                                                                                                                               | • # of sexual partners                                 | • Poisson: $\log(a)$
• Negative Binomial:
$\log(a/(k + a))$ |                                                                                                      |
| H 4                                                                                                                                                                                                               | • # of days in which no illicit
drugs were used     | • Poisson: $\log(a)$
• Negative Binomial:
$\log(a/(k + a))$ |                                                                                                      |
| H 5                                                                                                                                                                                                               | • Drug Treatment
Attendance/Engagement              | • Logistic:
$\log(a/(1 - a))$                                  |                                                                                                      |
| Candidate link functions (beyond distributional requirements) will be determined by selecting the function with the best overall fit metrics followed by statistical efficiency of the coefficient for study arm assignment. |                                                        |                                                                   |                                                                                                      |

**Power Analysis:** Power analyses were conducted using G\*Power (v3.1.0). Autocorrelation ( $\rho$ ) and ICC estimates were based on Project PACT trial and Pilot of Revised PACT in CCP settings. From ICC estimates, variance inflation factors were calculated to generate effective sample sizes. Outcome estimates for intervention effects were obtained from Project PACT while those for HIV CTR used PACT wellness promotion comparison condition as a proxy for non-specific attention. These estimates allow for effect size  $f^2$  to be calculated. For cumulative STI incidence, we assumed a 50% reduction to be clinically meaningful to detect via Poisson regression. Results for primary outcomes indicate that a minimum of 80% power is achieved for all primary outcomes with 96 couples per arm. Based on the team’s successful retention in Project WORTH with drug-involved offenders and prior couple-based studies for the likelihood of 80% to 85% retention, this is corresponding to 113 to 120 couples per arm (or a total of 226 to 240 couples) before 15% to 20% attrition. Power analyses with 96 participants per arm indicate 80% power to detect differences for effect sizes  $f^2 = .03$  to  $.04$  (for  $\rho = .1$  TO  $.5$ ), indicating the ability to detect substantially smaller than “medium” effect sizes (Cohen, 1988).

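### The hypotheses concern the 12-month follow-up, but the specified repeated-measures model has one arm coefficient and no arm-by-visit term, so it estimates an average over follow-up visits

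*Protocol*

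**What the plan says.** All of the following is in the protocol.

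- **Target.** Under Data Analyses, each hypothesis takes the form that assignment to PACT will be significantly "lower/higher on outcome variable Y at the 12-month follow-up compared to assignment to HIV CTR". This template covers H1 to H5.
- **Data entering the model.** The outcome is indexed by participant and timepoint. The GLMM is chosen partly to handle autocorrelation "due to repeated measures with the same person". Under Overview of subject participation, the self-report interview takes place at 3, 6 and 12 months, and follow-up STI specimens are taken at 6 and 12 months only.
- **Model components.** The coefficient vector is said to consist of "treatment assignment, baseline attributes for the outcome variable, and those variables selected during preliminary analyses as noted earlier". The Table 1 column headed "Covariates used to estimate" the coefficients lists baseline sociodemographics and the baseline value of the outcome. No visit term, arm-by-visit term or 12-month contrast is named.
- **Effect reported.** The note to Table 1 chooses between link functions by overall fit and then by "statistical efficiency of the coefficient for study arm assignment", which is a single coefficient.
- **H1.** Table 1 gives the outcome as incidence of the three infections. Power Analysis says: "For cumulative STI incidence, we assumed a 50% reduction to be clinically meaningful to detect via Poisson regression".

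**The concern.** The protocol fixes both the time point of the claim and the contents of the model, and the two do not match. In a repeated-measures model with one arm coefficient and no arm-by-visit term, that coefficient is a weighted average, on the link scale, of the arm differences at all visits that enter. It equals the 12-month difference only if the effect is the same at every visit.

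If the effect fades, the early visits can carry the coefficient to significance, and the result would be reported as a 12-month effect. If the effect emerges late, the early visits dilute it. Unless the choice is fixed before the data are seen, the quantity being tested can also be settled after the results are known.

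**Working it through.** **1. The plan's own figures.** Power Analysis gives 96 evaluable couples per arm and 15% to 20% attrition. 96/(1 − 0.15) = 112.9, so 113, and 96/(1 − 0.20) = 120, for totals of 226 and 240. These match. The plan also states 80% power at f² = .03 to .04. A noncentral F test with one predictor, N = 2 × 96 = 192 and two-sided 0.05 gives 78.7% at f² = .04 and 66.6% at f² = .03 (77.2% one-sided). The upper end agrees within 2 points. The lower end needs a larger effective N: a partner ICC of .5 would give 384/1.5 = 256, where 80% power is reached at f² = .031. The protocol gives no ICC, so the 96 itself cannot be rebuilt.

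**2. Inputs for the illustration.** From the protocol: 96 per arm, f² = .03 to .04, autocorrelation ρ = .1 to .5, visits at 3, 6 and 12 months. Assumed: two-sided alpha 0.05 (none is stated), normal outcomes, equal visit weights, equal correlation between visits, and the effect patterns themselves.

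**3. Formulas.** For two equal arms d = 2√f², so d = 0.346 or 0.400. The mean of three visits has variance v = (1 + 2ρ)/3 of a single visit: 0.400, 0.533 and 0.667 for ρ = .1, .3 and .5. SE = √(2v/96), and power = Φ(mean effect/SE − 1.96). For a 12-month contrast, v = 1.

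Worked example, effect d at 3 and 6 months and none at 12, f² = .03, ρ = .5: mean effect = 0.346 × 2/3 = 0.231; SE = √(2 × 0.667/96) = 0.118; ratio 1.96; probability of significance Φ(0) = 50.0%.

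**4. Results: probability that the single arm coefficient is significant.**

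| f² | ρ | Effect at 3 and 6 months only | Effect at 12 months only | Same effect at all visits |
|---|---|---|---|---|
| .03 | .1 | 71.6% | 24.4% | 96.7% |
| .03 | .3 | 59.1% | 19.4% | 90.8% |
| .03 | .5 | 50.0% | 16.4% | 83.6% |
| .04 | .1 | 83.2% | 30.9% | 99.2% |
| .04 | .3 | 71.6% | 24.4% | 96.7% |
| .04 | .5 | 61.9% | 20.4% | 92.4% |

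A 12-month contrast rejects at 5% in the first pattern. In the other two it has 67.0% power (f² = .03) or 79.1% (f² = .04). With a gradual decline (full effect at 3 months, half at 6, none at 12), the single coefficient is significant in 31% to 59%.

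**5. Second calibration.** Set the effect to give exactly 80% power at one visit, so that the expected z is 1.96 + 0.84 = 2.80. Then z for the pooled coefficient = mean pattern × 2.80/√v.

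- Effect at 3 and 6 months only: (2/3) × 2.80/√0.400 = 2.95, or 84%, at ρ = .1; (2/3) × 2.80/√0.667 = 2.29, or 63%, at ρ = .5.
- Effect at 12 months only: 1.48, or 31%, at ρ = .1; 1.14, or 21%, at ρ = .5; against 80% for the 12-month contrast.

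The two calibrations together give the quoted ranges: 50% to 84%, 16% to 31%, and 67% to 80%.

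**6. Cross-check.** A simulation with 4,000 runs per setting, baseline adjustment and the effect at 3 and 6 months only gave significance for the arm-only coefficient in 65% to 85% of runs. The 12-month contrast rejected in 4.7% to 5.7%.

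**7. STI.** Only the 6- and 12-month results exist, so the variance factor is (1 + ρ)/2. If visit-level results were modelled and the effect were present at 6 months only, the same normal approximation gives 28% to 46%. If H1 is analysed as cumulative incidence, this calculation does not apply.

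**The case against.** The best defence has four parts.

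- **The target is stated, and coding of visit belongs in the SAP.** The 12-month target is indeed clear, and contrast statements are often left to a SAP. Here, however, the protocol itself lists the components and refers to one arm coefficient. That is a conflict between two stated rules, not a missing detail.
- **The covariate vector is indexed by timepoint, and the list ends with variables selected in preliminary analyses.** The notation does allow a time term. But no such selection is described earlier in the text available, and Table 1 names only baseline variables. A visit main effect entering that way would still leave one arm coefficient and would not isolate month 12.
- **Perhaps only the 12-month record is analysed.** The protocol does not say so. Baseline is a covariate, so with one follow-up record per person the autocorrelation that the model is chosen to handle would have no role.
- **The effect patterns are hypothetical.** This stands. Nothing in the protocol says that the effect fades or arrives late, and the figures show what can happen, not what will.

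Two stronger readings are tempting and should not be drawn.

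- A reader might infer from the printed couple-level equation, which shows no random term, that within-couple and within-person correlation is ignored and type I error inflated. The equation follows "The multilevel nature of the data are accounted for by modeling each predictor variable's coefficient in the vector" and makes each coefficient depend on couple membership. But the protocol states that mixed models will account for both sources of correlation, presents the equation as something the models build on, and uses variance inflation for the ICC in Power Analysis. An error rate computed without clustering would describe a model that is not planned.
- A reader might infer that H1 loses much of its power because only the 12-month test counts. Table 1 says incidence and Power Analysis says cumulative, so incidence accumulated through the last visit is the natural reading. The loss would also rest on an invented split of events between visits.

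**Conclusion.** The point holds as a mismatch between the hypotheses and the model. Followed as written, the arm coefficient for the self-reported outcomes averages over 3, 6 and 12 months and does not test the hypothesis stated "at the 12-month follow-up compared to assignment to HIV CTR". For STI the average would be over 6 and 12 months, and only if visit-level results are modelled. The size depends on the true time course. With a constant effect the two quantities coincide and the average is the more precise. With an effect that has disappeared by 12 months, a false 12-month claim can have a probability of 50% to 84% instead of 5%. With an effect only at 12 months, power can fall to 16% to 31%. These ranges rest on the assumptions listed in the working: two-sided 0.05, normal outcomes, equal visit weights, equal correlation and chosen effect patterns. The outcomes are in fact counts and binary variables on a link scale, so the weights would not be exactly equal. The conclusion does not extend to the handling of clustering or to the power of H1.

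**What to change.** For the self-reported outcomes, choose one of two routes and fix it before outcome data are seen.

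- **Keep the 12-month hypotheses.** Add categorical visit (3, 6, 12 months) and arm-by-visit terms to the planned GLMM, keep its within-person and within-couple structure, and name the 12-month arm contrast as the test.
- **Keep the single arm coefficient.** Restate the hypotheses as arm differences averaged over follow-up, name the visits included, and make no separate 12-month claim from that coefficient.

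For H1, reword the hypothesis as cumulative STI incidence through 12 months, based on the 6- and 12-month tests, to agree with Power Analysis.

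The cost is wording only, with no new data or visits. The first route gives up precision if the effect is constant: in the illustration, 67% to 79% power for the 12-month contrast against 84% to 99% for the visit average.

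### H1 (STI incidence) has no fixed event unit or time window, and the rule for choosing between its logistic and Poisson models cannot supply one

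*Protocol*

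**What the plan says.** - The Assessment section makes biological assay for STIs part of the primary outcomes. Table 1 (Data Analyses) names H1 as "Incidence of Chlamydia, trichomonas and gonorrhea" and lists two candidates, logistic and Poisson. H2 to H4 are labelled as numbers of something and have Poisson and negative binomial candidates.
- The note under Table 1 says how the candidate is chosen: "selecting the function with the best overall fit metrics followed by statistical efficiency of the coefficient for study arm assignment".
- The general form of every hypothesis compares the arms as "lower/higher on outcome variable Y at the 12-month follow-up compared to assignment to HIV CTR".
- Overview of subject participation: "At the 6 and 12-month assessments biospecimens will be collected to test for STIs".
- Power Analysis: "For cumulative STI incidence, we assumed a 50% reduction to be clinically meaningful to detect via Poisson regression", with the claim that "a minimum of 80% power is achieved for all primary outcomes with 96 couples per arm".
- On correlation, Data Analyses says "Generalized Linear Mixed Models (GLMM) will be used to account for the non-independence in measures arising from" repeated measures in a person and partners in a couple. It adds "sensitivity analyses to ascertain robustness of findings against violation of model assumptions (e.g., distribution requirements, heteroscedasticity, independence").

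**The concern.** A primary outcome needs a rule that turns each person's results into one value. For H1 the protocol leaves two parts of that rule open.

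- **Event unit.** H1 could be whether a person was infected at all, or how many infections the person had.
- **Time window.** H1 could be status at 12 months, or everything found at 6 and 12 months together.

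The stated selection rule works on goodness of fit and on the precision of the treatment coefficient. Fit can compare models for one outcome, but it cannot choose between outcomes. The precision criterion is read from the data by arm.

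The same specimens could therefore give an odds ratio for being infected or a rate ratio for infections, each with its own p-value. The stated power would not clearly belong to either.

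**Working it through.** **1. The plan's own figures.** Enrolment reproduces: 96/0.85 = 112.9, so 113 couples per arm, and 96/0.80 = 120. The 80% power for STIs can be neither reproduced nor refuted, because the control-arm STI rate, the ICC and the significance level are not stated.

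**2. What the open definition does to the data.** Three organisms at two visits give up to 3 × 2 = 6 positives per person.

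| Person | Yes/no, cumulative | Count, cumulative | Yes/no, 12 months | Count, 12 months |
|---|---|---|---|---|
| Two organisms, both visits | 1 | 4 | 1 | 2 |
| One organism, 6 months only | 1 | 1 | 0 | 0 |

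Each column is compatible with some part of the text.

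**3. What the selection rule does.**

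- *If H1 is a count:* some people can score 2 or more. A binary logistic model cannot be fitted to that outcome, so there is nothing to compare.
- *If H1 is 0/1:* with a common risk p and no random effects, the Bernoulli log-likelihood exceeds the Poisson one by n[(1 − p)·log(1 − p) + p], which is always positive. Take n = 2 × 96 × 2 = 384 persons:
  - p = 0.10: 384 × 0.00518 = about 2 units
  - p = 0.20: 384 × 0.02149 = about 8 units
  - p = 0.30: 384 × 0.05033 = about 19 units

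  Fit then tends to favour logistic and to discard the Poisson model on which STI power was based.
- *If fit does not separate them:* the tie-break is precision of the arm coefficient. One coefficient is a log odds ratio and the other a log rate ratio, so their standard errors are not on a common scale. The choice also uses the data by arm.

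**4. What the stated power would require.** Assume two-sided 0.05, 80% power, a halving, and n = 192/(1 + ICC) effective persons per arm. The variance of the log ratio must be V = (0.693/2.802)² = 0.0612.

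- Count: V = 1/(nλ) + 2/(nλ) = 3/(nλ), so λ = 3/(nV).
- Yes/no: V = (3/p − 2)/n, so p = 3/(nV + 2).

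| ICC (assumed) | n | Infections per control person (count) | Control persons infected (yes/no) |
|---|---|---|---|
| 0 | 192 | 0.26 | 22% |
| 0.3 | 147.7 | 0.33 | 27% |
| 0.5 | 128 | 0.38 | 31% |

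The two readings need different control rates. The effect scale differs too: a fall from 22% to 11% is a risk ratio of 0.50 but an odds ratio of (0.11/0.89)/(0.22/0.78) = 0.44.

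**5. Cost of the freedom.** This was simulated under no effect, with 96 couples per arm, six tests per person, an assumed 3% or 5% positive per test, and latent couple and person correlation. The cumulative count and the cumulative yes/no outcome were each tested on the log scale with couple-clustered standard errors. The chance that at least one was significant at 5% was about 7% to 8% with correlation and 6% to 7% without. Part of the excess is the count test's own size, about 6% in the more correlated settings.

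**The case against.** The strongest reply is that Table 1's column lists candidate link functions, and H1 is labelled incidence while H2 to H4 are labelled as numbers. H1 may then be one yes/no outcome with two candidate links, and a Poisson model with a log link can serve a yes/no outcome. That reading is possible, so the two candidates do not prove that two outcomes were intended. It still leaves the time window open. It also leaves the selection rule favouring a model other than the one used for power, with the arm coefficient as tie-break.

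A second reply is that such detail belongs in the SAP, which is not at hand. A counting rule alone could be left there. Here, however, the protocol itself fixes how the choice is made, and that rule cannot do the job.

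A reader might go further and infer that Poisson standard errors would be wrong whichever definition is used. The documents do not support this. The plan specifies a mixed model for person and couple correlation, not a plain Poisson test, and adds sensitivity analyses on distribution and independence. A Poisson mixed model with a couple random intercept, simulated under assumed rates and correlations (500 runs per scenario, Monte Carlo error about 1 point), had size 4.2% to 7.2% for counts and 3.2% to 5.6% for yes/no.

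Nor does a logistic model test a different null: without covariates, an odds ratio of 1 and a risk ratio of 1 are the same statement. What changes is the effect reported and its match to the planned 50% reduction.

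**Conclusion.** The point holds as a defect of definition and of model selection. H1 has no stated event unit, its time window differs between the hypothesis form and the power section, and the rule given for choosing the model cannot resolve either.

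The size is moderate. The figure of about 8% instead of 5% is an upper bound, reached only if the more favourable version is chosen, and it rests on assumed test positivity and correlations. The control rates needed for 80% power rest on an assumed two-sided 0.05 and assumed ICCs. They show that the power claim cannot be tied to one endpoint, not that it is false. The log-likelihood gains ignore random effects.

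**What to change.** Define H1 once, in the same words in Table 1 and Power Analysis. One workable definition is, per participant, any new positive for any of the three organisms at the 6- or 12-month test. It needs a stated rule for infections already present at baseline, because counting every positive would include persisting infections in an outcome called incidence.

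Analyse it with one pre-specified log-link model and couple-clustered robust variance, so that the ratio tested is the planned 50% reduction. Robust variance is useful because a random intercept can only add variance and cannot correct for 0/1 data varying less than Poisson. Drop the fit and efficiency selection for H1. State the control-arm risk, ICC and significance level behind the STI power. Report the number of infections and each organism as supportive results.

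The cost is a change of wording, with no new data. The downside is that repeat and multiple infections in one person no longer add to the main test.
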